### **2.3 Exploratory**

*2.3.1 To describe signals of improvement in food insecurity, nutrition insecurity, cost-coping behaviors, parent role satisfaction and financial well-being.*

*2.3.2 To describe participants’ thoughts about MTM-Kids processes, the meals, and recommended improvements.*

---

### **3 STUDY ENDPOINTS**

#### **3.1 Primary Endpoint**

- 3.1.1 *Feasibility of recruitment and retention of a study sample for a future efficacy trial of MTM-Kids intervention to mitigate food-related insecurities for households of adolescents in active treatment with chemotherapy for pediatric cancer is defined as 70% enrollment, 70% completion of baseline and Week 12 surveys, and 70% receipt of at least 4 weeks of meal deliveries + completion of at least one interview by adolescent and by parent (either week 4, 8 or 12)*

#### **3.2 Secondary**

- 3.2.1 *Participant-reported acceptability, appropriateness, feasibility, affordability, and accessibility of the MTM-Kids intervention is defined as mean overall scores for the 4 item measures of each domain (appendix X)  $\geq 3$  (agree) for 70% of adolescents (acceptability and appropriateness) and 70% of parents (acceptability, appropriateness, feasibility, affordability, and accessibility) at week 12 (T4).*

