### **6.3 Participant Withdrawal**

If an adolescent or parent decides to withdraw from the study (and not just from the protocol intervention) an effort should be made to complete and report study assessments as thoroughly as possible. At the time of withdrawal, the investigator should attempt to establish as completely as possible the reason for the study withdrawal.

---

- A complete final evaluation at the time of the participant's study withdrawal should be obtained with an explanation of why the participant is withdrawing from the study.
- If the participant is noncompliant and does not show up for an end of study follow up assessment, this should be documented in the eCRF.

Excessive participant withdrawals from protocol intervention or from the study can render the study not feasible therefore, unnecessary withdrawal of participants should be avoided.

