#### 7.2.1 *Surveys and Interview Questions for Adolescents*

Adolescents will be asked to complete (a) a brief investigator-developed socio-demographic survey at baseline (T1), (b) established measures of alterations in taste and chemotherapy induced alterations in taste at weeks 4, 8, and 12 (T2-4) at the start of their semi-structured interviews, and (c) a person-reported measure of acceptability and appropriateness at week 12 (T4).

Socio-demographic items will ask the adolescent to tell us their current age (in years), sex at birth, race, the language they mainly use at home, and their current grade (year) in school.

---

Chemotherapy-induced alterations in taste will be measured by 13-items from the Chemotherapy-Induced Alterations in Taste Scale (CiTAS) [50]. Adolescents will be asked to use a 5-point scale to indicate how much the taste change bothered them this week. Scores will be calculated by summing item responses and dividing by 13 (lower scores indicate less alteration in taste).

Other chemotherapy-related symptoms will be measured by the 15-item Symptom Screening in Pediatrics (SSPedi) tool. [51] Adolescents will be asked to use a 5-point scale anchored by 0 (not at all) and 4 (worst bother) to indicate how much each symptom bothered them today or yesterday. Scores will be calculated by summing item responses. Scores can range from 0-60; lower scores indicate less symptom severity.

Semi-structured interviews will focus on the adolescent's experience with a study provided meal and their recommendations for improvements.

Adolescent-reported acceptability and appropriateness of the MTM-Kids program will be assessed using items that tap into each of these domain. The original items were developed and validated by Weiner and colleagues for use in studies that examine adopters' perspectives on the acceptability, etc. of implementing entire evidence-based programs in practice.[52] For this feasibility study, the Weiner, et al. items served as the basis for assessing areas that may affect participants' perspectives on specific aspects of the MTM program. Each domain has 4-items. Adolescents will be asked to read each item and indicate their response using 5-point scales anchored by 1=completely disagree and 5=completely agree. Domain scores will be calculated by summing item responses and dividing the sum by 4. Domain score range is 1-4, with higher scores indicating better acceptability or appropriateness.

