### 8.1 Study Design

This feasibility study uses a longitudinal design and multiple methods to determine the possibility of using the MTM-Kids study processes and intervention in a future full-scale RCT. 15 parent/adolescent dyads will be enrolled and asked to complete a survey at baseline (T1), receive MTM-Kids meals over 12 weeks, participate in interviews at 4, 8, and 12 weeks (T2, T3, T4) after starting to receive meals to inform refinement, and complete a follow-up survey at 12 weeks (T4).

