## **8.3      Data Analysis Plans**

### **8.3.1      *Primary Endpoint Analysis***

For project to be considered successful and feasible in a larger study, we determined the following benchmarks: a) 70% of those approached are enrolled in the study, (b) 10 out of 15 participating parent/adolescent dyads should complete the baseline and week 12 surveys, (c) 10 out of 15 parents receive at least 4 weeks of meal deliveries, and (d) in 10 out of 15 dyads, the adolescent and the parent each complete at least one interview (week 4, 8, or 12). We will estimate the retention rate and report it with a 95% confidence interval.

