### **8.3.2      *Secondary Endpoint Analysis***

Descriptive statistics (mean, standard deviation [SD], score range) of the measures of adolescent acceptability and appropriateness as well as parental acceptability, appropriateness, feasibility, affordability and accessibility at week 12 will be reported.

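### Section 3.2.1 sets a 70%-of-individuals criterion at week 12, but Section 8.3.2 lists only mean, SD and range, which cannot show whether it was met; the base of the 70% is also unstated

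*Protocol*

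**What the plan says.** - **Endpoint.** Protocol 3.2.1 sets a threshold on each person's domain score (at least 3) and asks for a share of people reaching it: "agree) for 70% of adolescents (acceptability and appropriateness") and "70% of parents (acceptability, appropriateness, feasibility, affordability, and accessibility) at week 12 (T4"). It does not say whether the share is of those enrolled or of those who answer.
- **Timing.** Section 7.2.1 schedules the adolescent form once, as "a person-reported measure of acceptability and appropriateness at week 12 (T4"). The parent endpoint is also fixed at week 12.
- **Analysis.** Section 8.3.2 names the mean, SD and score range of the five parent and two adolescent domains; these are what for "accessibility at week 12 will be reported". No count or percentage at or above 3 is listed.
- **Sample and retention.** Under Section 8.1, "15 parent/adolescent dyads will be enrolled". Section 8.3.1 accepts that "10 out of 15 participating parent/adolescent dyads should complete the baseline and week 12 surveys", while Section 3.1.1 asks for "70% completion of baseline and Week 12 surveys".
- **People who leave.** Section 6.1 asks those who stop the intervention whether later scheduled assessments may still go ahead. Section 6.3 calls for a final evaluation at withdrawal, which "should be obtained with an explanation of why the participant is withdrawing from the study". It does not name the acceptability form.

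**The concern.** An endpoint framed as a proportion of people needs a proportion in its analysis. If Section 8.3.2 is followed as written, the report will hold group averages and spreads, and the reader will be unable to tell whether 70% was reached in any domain.

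The unstated base adds to this. The rating is tied to the last time point of a study that allows a third of its dyads not to complete the surveys. When raters are fewer than enrolled, the same data can pass on one base and fail on the other, and the choice would be made after the data are seen. Section 1.2 lists acceptability and appropriateness among the uncertainties to be settled before deciding on a definitive trial, so the figure will be used.

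**Working it through.** **Inputs.** 15 dyads enrolled (8.1); at least 10 of 15 dyads completing the baseline and week 12 surveys (8.3.1) or 70% (3.1.1); domain score of at least 3 in 70% (3.2.1); domain score equal to the sum of four items divided by 4 (7.2.1, 7.2.2), so scores move in steps of 0.25.

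**Step 1: the plan's own retention figure.** 10/15 = 66.7%. Section 3.1.1 implies 0.70 × 15 = 10.5, hence 11 dyads (11/15 = 73.3%). The two sections differ by one dyad, and this matters in Step 3.

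**Step 2: can the listed statistics show the criterion?**

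- *Mean alone.* Four scores of 5.0 and six of 2.75: (4 × 5.0 + 6 × 2.75)/10 = 36.5/10 = 3.65. The average is well above 3, yet only 4/10 = 40% reach 3.
- *Mean, SD and range together* (constructed illustration, ten raters):

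| | Set A | Set B |
|---|---|---|
| Scores | 2.0 ×2, 2.75 ×4, 4.0 ×4 | 2.0 ×3, 3.25 ×4, 4.0 ×3 |
| Sum | 4 + 11 + 16 = 31 | 6 + 13 + 12 = 31 |
| Sum of squares | 8 + 30.25 + 64 = 102.25 | 12 + 42.25 + 48 = 102.25 |
| Mean | 3.1 | 3.1 |
| SD = √[(102.25 − 31²/10)/9] | √(6.15/9) = 0.83 | 0.83 |
| Range | 2.0 to 4.0 | 2.0 to 4.0 |
| At or above 3 | 4/10 = 40% | 7/10 = 70% |

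Every statistic in 8.3.2 is identical, while Set A fails the criterion and Set B meets it.

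**Step 3: what the base does.** With k raters, the fewest needed for 70% of raters is 0.70 × k rounded up; dividing by 15 gives the share of those enrolled.

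| Raters k | Needed | Share of raters | Share of 15 enrolled |
|---|---|---|---|
| 8 | 6 | 75.0% | 40.0% |
| 10 | 7 | 70.0% | 46.7% |
| 11 | 8 | 72.7% | 53.3% |
| 12 | 9 | 75.0% | 60.0% |
| 13 | 10 | 76.9% | 66.7% |
| 14 | 10 | 71.4% | 66.7% |
| 15 | 11 | 73.3% | 73.3% |

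Exact (Clopper-Pearson) 95% intervals: 7/10, 35% to 93%; 7/15, 21% to 73%; 11/15, 45% to 92%.

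On an all-enrolled base with non-raters counted as not meeting the threshold, 11 of 15 are needed. With 10 raters even a unanimous result (10/15 = 66.7%) falls short.

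**Step 4: replacement.** Section 5.4 allows people who leave before being evaluable to be replaced, so the number enrolled may exceed 15. Assuming 1 to 5 replacements, 7 who meet the threshold are 7/16 = 43.8% down to 7/20 = 35.0% of those enrolled.

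**The case against.** **Proportions are planned elsewhere.** The opening of Section 8 announces proportions and confidence intervals for the feasibility benchmarks set in advance. That is a fair point, but the sentence refers to the Time & Events Table, which contains no benchmarks. The benchmarks in 8.3.1, (a) to (d), do not include acceptability. The section written for this endpoint leaves the proportion out, so the mismatch stands.

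**Denominators and missing ratings belong in the SAP.** Largely right, and an SAP not shown here may settle the base. The mismatch between 3.2.1 and 8.3.2 lies within the protocol and does not depend on it.

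**A stronger reading is tempting:** that the plan rates only those who stay, that dissatisfied families are the ones who leave, and that the criterion will therefore be declared met with under half of those enrolled in favour. The documents do not support this.

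- No section states a completers-only base, and reporting means does not by itself cause the criterion to be declared met.
- Sections 6.1 and 6.3 seek data from people who stop or withdraw.
- Nothing shows that dislike of the meals drives departure; Sections 6.1 and 6.5 also foresee leaving through a change in the child's condition or death.
- A share under half needs 10 or fewer raters. Under the 70% rule of 3.1.1 the lowest passing share is 53%.
- The 8.3.1 benchmark counts dyads. Ten complete dyads give at least ten raters in each role, and possibly more.

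**Counting every non-rater as a failure mixes retention into acceptability.** This stands. Retention is already the primary endpoint, and ten favourable ratings out of ten would fail for attrition alone.

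**Conclusion.** The analysis in Section 8.3.2 does not deliver the endpoint in Section 3.2.1. This follows from the text and needs no assumption about drop-out: identical means, SDs and ranges are compatible with 40% or 70% meeting the threshold.

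The open base is a second, conditional weakness. It changes nothing if all 15 rate. At 10 raters it separates 70% from 47%, and at 11 raters 73% from 53%. These figures assume 15 enrolled, no replacements and no ratings from non-completers.

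The protocol does not establish that ratings will be biased upward or that a completers-only verdict is intended. The point warrants a correction before analysis but does not threaten the study: this is a descriptive secondary endpoint outside the success benchmarks of 8.3.1. The threshold of 3 is taken here as written; whether it means agreement on the five-point response scale is a separate matter.

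**What to change.** 1. **Section 8.3.2.** For each domain and each role, report the number and percentage meeting the 3.2.1 threshold with an exact 95% CI, both among raters and out of all enrolled, and list the reasons for non-rating. Keep the mean, SD and range as supplementary description.
2. **Sections 3.2.1 and 8.3.2.** State in advance which base is compared with 70%, and whether replaced participants count as enrolled. Show the figure that counts non-raters as not meeting the threshold as a conservative bound, not as the sole verdict.
3. **Section 6.3.** Name the acceptability form as part of the evaluation at withdrawal, and report those ratings separately from week 12 ratings, since they refer to a different time point.

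**Cost.** A few sentences, one extra table column and a short existing form at withdrawal. The all-enrolled figure may look less favourable, particularly when people leave because of illness; the listed reasons let the reader judge that.

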#### **3.3 Exploratory**

- 3.3.1 *Signals of improvement in food insecurity, nutrition insecurity, cost-coping behaviors, time demands, and financial well-being is defined by improvements in T4 (post intervention) measurements as compared to T1(baseline pre-intervention).*
- 3.3.2. *Adolescent and parent thoughts about MTM-Kids processes, the meals, and recommended improvements in the meals and study processes are defined as themes that emerge from analyses of qualitative interviews with the adolescents, and with their parents.*
-

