Food is Medicine interventions (conjunctions of food and healthcare that aim to increase access to nutritious food and thus support health)[44] include offering: (a) prescriptions for produce (vouchers for food items that may require preparation), (b) medically tailored groceries (food items that may require preparation), and (c) MTMs (home-delivered, ready to heat-and-eat meals designed by a registered dietician).[44] MTMs are the most intensive type of Food is Medicine intervention, indicated for persons with substantial physical and/or contextual barriers to preparing healthy meals. Contextual barriers apply to households in which parents navigate the caregiving demands of serious pediatric illness. Short term MTMs (high risk pregnancy), or long-term MTMs (AIDS, diabetes, organ failure) improve outcomes and reduce health care costs for adult populations with SDOH inequities. [25, 44] To our knowledge, MTM interventions have not been tested in pediatric serious illness populations for which nutrition is a known, important predictor of treatment success, long-term health, and well-being. Historically, needs of pediatric populations have received little attention – children lack political clout and thus disparities for pediatric populations persist.[45] This study is a first step towards system-level interventions that embed equity into holistic care delivery for pediatric populations with serious illness. Areas of uncertainty to be addressed by this feasibility study prior to deciding whether to proceed with a future definitive trial [46] include the (a) feasibility of recruiting and retaining a sample; (b) feasibility of MTM ordering and delivery, and acceptability, affordability, accessibility, and appropriateness of MTM for the target population, and (c) sensitivity of proposed pathways to MTM.

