## 8 STATISTICS

We will calculate descriptive statistics (frequency, proportion, central tendency, range, standard deviation [SD], reliability) to describe the study sample and estimate proportions, odds ratio, and confidence intervals (CI) for a priori feasibility benchmarks (see Time & Events Table). Feasibility study data can provide unreliable effect size estimates given small sample sizes. [46, 58] Thus, we will follow Brown [59] and estimate SDs and CIs for signals of change in food-related insecurities, cost-coping, time demands and QOL and use upper limits of 80% CIs plus enrollment and retention data to estimate sample size for the future efficacy trial. We will also consider evidence for associations between improvement in food security and QOL from studies of MTM with adult populations in estimating sample size for the future trial. [11, 44] Within days of an interview, two coders per interview will use rapid qualitative content analysis to analyze verbatim transcripts, compare their results and engage in discussion to resolve any discrepancies. The conceptual model (Figure 1) will guide the rapid analysis.[60] The goal is to identify actions at multiple levels (meal, child, household, study) to inform refinements for validation testing and ultimately the protocol for the future trial. When all interviews have been completed, we will use traditional content analysis to identify themes in the data overall to inform further refinements.

To ensure a rigorous and reproducible study, we have taken the following steps:

- Established a plan to enroll a diverse sample
- Justified the sample size
- Selected established measures to measure study variables
- Established the data analysis plan prior to data acquisition
- Considered relevant biological variables

Because sex hormones can affect taste function, processing of sweet and bitter, and food acceptability, [61] we will enroll similar numbers of biological female and male adolescents for each aim and explore the role of biological sex in the quantitative and qualitative data about alterations in taste and meal acceptability.

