### **8.3.3      *Exploratory Endpoint Analysis***

Descriptive statistics (mean total scores, score ranges, standard deviations) and figures will be used to portray the results of baseline (T1) and 12 weeks (T4) assessments of household food insecurity, household nutrition insecurity, parental financial coping strategies, parental time demands, and parental financial wellbeing.

Descriptive statistics (mean total score, score range, SD) will be used to portray adolescents' treatment-related symptoms and chemotherapy-induced alterations in taste.

Qualitative descriptive approaches will be used to identify themes in the interviews with adolescents and parents about their experiences with MTM-Kids meals and recommendations for needed improvements.

---

Treatment exposures, scores on assessments of symptom and chemotherapy induced alterations in taste will be used to qualitatively explore linkages between symptoms, alterations in taste, and themes in the interview data.

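### Section 3.3.1 defines a signal of improvement by direction alone, and 8.3.3 reports separate T1 and T4 summaries instead of within-parent change with the interval that section 8 plans (minor)

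*Protocol*

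**What the plan says.** Protocol section 2.3.1 sets a descriptive aim: "To describe signals of improvement in food insecurity, nutrition insecurity, cost-coping behaviors, parent role satisfaction and financial well-being". Section 3.3.1 turns it into an endpoint. It lists five outcomes, "Signals of improvement in food insecurity, nutrition insecurity, cost-coping behaviors, time demands, and financial well-being", and the sentence ends with the definition: "financial well-being is defined by improvements in T4 (post intervention) measurements as compared to T1(baseline pre-intervention". It gives no minimum size and no interval, and does not say whether the group mean or the individual parent is meant.

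Section 8.3.3 gives the analysis: "Descriptive statistics (mean total scores, score ranges, standard deviations) and figures will be used to portray the results" at T1 and at T4. It does not name the within-parent change.

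The opening of section 8 goes further. It warns that small feasibility samples give unreliable effect sizes. It then plans to "estimate SDs and CIs for signals of change in food-related insecurities, cost-coping, time demands and QOL", and to use upper limits of 80% intervals in sizing the later trial. That list includes QOL, which is not among the measures in the Time & Events Table, and omits financial well-being, which is one of the five outcomes in 3.3.1.

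Section 1.2 names "sensitivity of proposed pathways to MTM" among the uncertainties to be addressed before deciding on a definitive trial. The success benchmarks in 8.3.1 cover enrolment, survey completion, meal deliveries and interviews only.

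**The concern.** A definition based only on direction takes no account of chance. With 10 to 15 parents, a mean score moves one way or the other even if nothing has changed, and a favourable move meets the wording of 3.3.1. Five outcomes give five opportunities for this.

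Separate T1 and T4 summaries add a second problem. Benchmark (b) in 8.3.1 accepts 10 of 15 dyads completing both surveys. The T1 mean may then rest on 15 parents and the T4 mean on 10, and the difference mixes change with who stayed.

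What is at stake is how the pathway results are read when a definitive trial is considered. A report that several outcomes showed signals of improvement could carry weight that direction alone does not support.

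**Working it through.** The protocol states no error rate or power for this endpoint, so there is no figure of its own to reproduce.

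**Inputs from the protocol.** Five outcomes (3.3.1), all reported by the same parents (7.2.2); 15 dyads (8.2.1); 10 of 15 completing both surveys is acceptable (8.3.1); single arm (Study Summary); a food insecurity score that counts 0 to 6 affirmative answers (7.2.2).

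**Assumptions not in the protocol.** The group mean is what is compared; mean changes are symmetric about zero when nothing changes; between-outcome correlation runs from 0 to 0.7; T1–T4 correlation is 0.5 or 0.7.

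**1. One outcome, no change.** For a symmetric continuous change, P(favourable mean) = 0.50. On a simulated 0–6 count with n = 10 or 15, it is 0.46–0.47, because 6–9% of studies give an exact tie.

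**2. At least one of five, no change.** If independent: 1 − 0.5⁵ = 1 − 0.03125 = 0.969. With equal correlation ρ (equicorrelated normal model, numerical integration):

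| ρ | at least one of five |
|---|---|
| 0 | 0.97 |
| 0.3 | 0.90 |
| 0.5 | 0.83 |
| 0.7 | 0.76 |

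**3. A real change, by direction alone.** For a true mean change of d standard deviations of change, P(favourable) = Φ(d√n). At d = 0.5: n = 10 gives Φ(1.58) = 0.94; n = 15 gives Φ(1.94) = 0.97. So direction carries some information per outcome: 0.50 against 0.94–0.97.

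**4. Dropout illustration.** Suppose ten households score 2 and five score 5 on the 0–6 count at T1. The T1 mean is (10 × 2 + 5 × 5)/15 = 45/15 = 3.0. If the five leave and the ten do not change, the T4 mean is 2.0. The summary shows an improvement of 1.0 although no household improved. In the ten pairs the mean change is 0.

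**5. The same data read with a paired 80% interval.** With no change, the interval lies wholly on the favourable side in 10% of studies per outcome. At least one of five: 1 − 0.9⁵ = 0.41 if independent, 0.34 at ρ = 0.3, 0.29 at ρ = 0.5 and 0.24 at ρ = 0.7. With a true change of 0.5 standard deviations of change, the interval clears zero with probability 0.589 (n = 10) or 0.725 (n = 15), from the noncentral t. It therefore fails to do so in 1 − 0.589 = 41% or 1 − 0.725 = 28% of studies.

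**6. Drift through selection.** Section 5.1 requires a positive hardship screen. In a simulation with no effect and a screener correlated 0.6 with the outcome (assumed), the direction-only rate is 0.72–0.83 per outcome.

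**The case against.** The strongest reply is that this is no decision rule. The objective is to describe, 8.3.3 is descriptive, no benchmark in 8.3.1 uses a signal, and section 1.2 attaches no threshold to pathway sensitivity. The protocol never counts signals across outcomes, so the at-least-one figure is a reader's construction. All of this stands, and it makes the point minor. It does not remove the weakness in the definition, because 3.3.1 does fix what counts as a signal.

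Second, section 8 already plans intervals for the signals of change; sizing the later trial is an additional use. This also stands. A reader might infer that the protocol wants intervals only for sizing, and the text does not support that. The gap is that 3.3.1 and 8.3.3 do not link to those intervals, and that the section 8 list does not match the five outcomes.

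Third, the choice of analysis set and the handling of incomplete pairs often belong to a statistical analysis plan, which is not at hand. That is fair as to detail. The point here is only that the summaries 8.3.3 does name are separate ones.

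Fourth, drift need not favour improvement. A household can qualify on utility or transportation hardship alone; section 1.2 expects a further 15% of households to fall into poverty in the six months after diagnosis; and the cost-coping questionnaire asks about the whole period since diagnosis, so T4 includes the T1 period. This stands, and the direction of drift is unknown.

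Two stronger readings are tempting. One is that some outcome will almost always show a signal; that needs nearly independent outcomes, and the same parents report on linked household matters. The other is that the definition cannot separate an inert programme from an active one; step 3 shows that this is too strong for a single outcome.

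**Conclusion.** The point holds as a minor fault of definition and reporting. Read as a comparison of group means, 3.3.1 labels an outcome improved in about half of studies with no change, and labels at least one of five improved in about 76% to 97%. These figures rest on symmetric mean changes and an assumed between-outcome correlation of 0.7 to 0, which the protocol does not give. Separate T1 and T4 summaries can also move through dropout alone; how far depends on who leaves, which is unknown. No formal success criterion is affected. The consequence is confined to how the exploratory results are read when the definitive trial is considered under section 1.2.

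**What to change.** In 3.3.1, define the signal as the mean within-parent T4-minus-T1 change among parents with both assessments, presented with its 80% confidence interval. In 8.3.3, report for each of the five outcomes the number of pairs, the paired mean change, its SD and its 80% interval, and compare T1 with T4 only in those pairs. Describe a favourable change whose interval includes zero as inconclusive. State that change in a single arm of households selected on hardship cannot be attributed to the meals. In section 8, align the list with 3.3.1: add financial well-being, and either name a QOL measure or remove the term.

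This needs wording only, no new data, and section 8 already uses the 80% level. The cost is that fewer outcomes will be described as improved: for a true change of 0.5 standard deviations of change, the interval would fail to clear zero in about 28% (n = 15) to 41% (n = 10) of studies. For that reason the interval should be presented as a description and not made a pass/fail test on 10 to 15 parents. It does not remove drift either, so the attribution statement is needed as well.
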